**Acceptability**				
***Retention rate***	Number of clients and counselors who drop out of the intervention	X	X	X
***Safety***	Number of adverse events reported to the IRB	X	X	X
***Satisfaction***	Acceptability of Intervention Measure [63]		X	X
**Fidelity** ***Adherence to PST techniques***	Friendship Bench Fidelity Checklist assessed via audio recordings (if consented) ^‡^			

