#### Implementation outcomes

We will quantitatively assess feasibility outcomes, acceptability, and fidelity. All feasibility metrics are summarized in Table 3. Acceptability will be measured by evaluating retention rate (i.e., number of participants and lay counselors who drop out of the intervention) and safety (i.e., number of adverse events reported to the Institutional Review Board). To assess the acceptability of the intervention from the perspective of participants, we will use the Acceptability of Intervention Measure [63]. AIM is a 4-item scale that captures participants’ overall perceptions of the intervention’s acceptability, using a 5-point Likert response format. These items assess whether participants found the intervention appealing, satisfactory, and appropriate. Acceptability will also be measured through semi-structured interviews with participants and lay counselors as described below. This mixed-method approach (close- and open-ended items) will provide both quantitative and qualitative data on acceptability and identify areas for improvement in future implementation. All qualitative metrics are captured in Table 3.

Lay counselor adherence to the protocol will be monitored using a fidelity checklist and weekly supervision sessions. Fidelity will capture lay counselors' adherence to core problem-solving therapy techniques. Fidelity will be assessed through audio recordings of counseling sessions, contingent upon participant consent, as individuals may choose to opt out of being recorded. During the initial phase of implementation (within the first 2 weeks), all the sessions will be reviewed in a timely manner to provide formative feedback and support counselor development. A random sample of approximately 20% of recorded sessions will be evaluated thereafter.

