#### Referral and safety protocols

The adapted intervention includes a built-in referral pathway to connect participants with available HIV- and GBV-related services. This ensures ethical linkage to care for individuals experiencing ongoing violence or HIV risk. Our referral pathway is integrated into the adapted intervention design. Lay counselors and study staff will be equipped to refer participants to existing HIV- and GBV-related resources such as One Stop Centres and clinic-based HIV counseling and testing services. One Stop Centres are facilities—often located within government hospitals or clinics—that offer comprehensive services for individuals affected by GBV, including medical care, psychosocial support, legal assistance, and police services. Given recent reductions in U.S.-funded HIV and GBV programs, the availability of services may vary. Therefore, referral pathways will be documented and regularly reviewed in collaboration with local partners to ensure appropriate linkage to care. This referral process aligns with our ethical responsibility to support participants beyond the scope of counseling sessions.

Similar to the pilot trial of the Friendship Bench in Zimbabwe, participants who present with suicidal ideation or do not show clinical improvement during or after the six sessions will be referred to a mental health clinician or supervisor for additional support and possible referral to specialized care. In the original pilot, fewer than 10% of individuals who screened positive for common mental disorders were referred to a mental health specialist, primarily due to suicide risk or very severe symptoms identified at screening [73]. Additionally, we will record all safety events such as suicidality, worsening symptoms, and non-suicidal self-injury (i.e., self-cutting and burning). Though not likely, if rates of suicidal ideation increase beyond baseline levels, there will be an automatic study pause for ethics review. Stopping rules include halting the study in cases of severe emotional distress among 10% of participants or more at any point during implementation of the study, unforeseen harm, ethical or legal violations, or when potential harm outweighs benefits.

Adverse events will be documented by study staff and reviewed by the PI. Serious adverse events, including suicidality, will trigger immediate referral per the safety protocol and be reported to the UCLA IRB and UNZABREC.

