#### Data privacy, protection, and sharing

All participant information will be de-identified by assigning subject ID numbers in place of names. Lay counselors will sign confidentiality agreements, and data will be stored securely using REDCap. Audio recordings, accessible only to the study team, will be destroyed 2 years after the study ends. We will publish study findings without using participant names. All quantitative data will be entered into REDCap. Data entry will include built-in range checks in REDCap, and research staff will conduct double-checking for accuracy.

Access to the final trial dataset will be restricted to the Principal Investigator and designated study team members. There are no contractual agreements that limit investigator access. After study completion, de-identified data may be made available upon reasonable request to the corresponding author with appropriate ethical approvals.

Study oversight is maintained by the PI (the first author) and IRBs. There is no separate steering committee or endpoint adjudication team for this trial. The PI and Co-Investigators will oversee all aspects of implementation and data management. Internal auditing will be conducted by the research coordinator, with oversight and periodic review by the PI to ensure protocol adherence and ethical conduct. No independent data monitoring committee (DMC) is used for this RCT given its small sample size and minimal risk design.

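### The safety outcome counts adverse events reported to the IRB, but reporting there is stated only for serious events, so recorded non-serious harms may go uncounted

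*Protocol article*

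**What the plan says.** The outcome is defined twice in the protocol article, in matching terms. In Table 1, under Acceptability, the Safety row reads "Number of adverse events reported to the IRB" and is marked at baseline, 3 months and 6 months. The Implementation outcomes section gives safety as the "number of adverse events reported to the Institutional Review Board" and treats it as one component of acceptability.

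The Referral and safety protocols section describes what is collected and where it goes:

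- Recording: "we will record all safety events such as suicidality, worsening symptoms, and non-suicidal self-injury".
- Handling of adverse events in general: "Adverse events will be documented by study staff and reviewed by the PI".
- Reporting to the boards: "Serious adverse events, including suicidality, will trigger immediate referral per the safety protocol and be reported to the UCLA IRB and UNZABREC".

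On oversight, the section on data privacy, protection and sharing states: "No independent data monitoring committee (DMC) is used for this RCT given its small sample size and minimal risk design".

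**The concern.** The outcome is filtered by a reporting route, and the only route to the boards that the article describes is for serious events. What is recorded is broader than that. If the rules are followed as written, an event such as symptom worsening or distress that nobody classes as serious is documented, reviewed by the PI, and then not counted in the safety outcome.

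This matters because the harms the protocol itself foresees are of a kind that need not be serious. The section on informed consent and risk minimization names distress and the stirring up of past trauma, and the section on religious context and setting adds re-traumatization in church spaces. Safety is also something the authors intend to conclude on: the Hypothesis section expects the trial to show feasibility, acceptability and safety like those of an earlier feasibility trial, and acceptability belongs to Aim 2. A count narrowed by reportability leans towards that expectation. With no independent monitoring committee and adverse events reviewed by the PI, the reported count is the main quantitative statement on harm that readers will see.

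**Working it through.** No arithmetic is needed and the article states no figure to reproduce. The check sets the outcome definition beside the collection and reporting rules.

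1. **What is counted.** Table 1 and Implementation outcomes agree: adverse events reported to the IRB. Because both places say the same thing, this is a stated choice and not detail left for an analysis plan.

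2. **What is recorded.** Referral and safety protocols: all safety events, with suicidality, worsening symptoms and non-suicidal self-injury as examples.

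3. **What is stated to reach the boards.** Same section: serious adverse events, including suicidality. For adverse events in general, the stated route is documentation by staff and review by the PI, with no mention of the boards.

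4. **Comparison by type of event, on the stated text.**
   - Suicidality: recorded, named as serious, reported, counted.
   - Worsening symptoms: recorded; counted if classed as serious, otherwise no stated route into the count.
   - Non-suicidal self-injury: as for worsening symptoms.
   - Distress from discussing trauma: recorded if treated as a safety event; counted only if classed as serious.

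5. **Is it counted elsewhere?** No other row of Table 1 counts adverse events. The referral rate counts referrals. The symptom scales (SSQ-14, PHQ-9, GAD-7, CPSS) measure levels at visits. The Burden domain in Table 3 is qualitative. The stopping rules are triggers for halting, not a reported outcome.

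6. **Size.** Let R be all recorded adverse events, S those classed as serious, and N the non-serious events that reach a board by some route the article does not describe. The outcome counts S + N, and the omitted share is (R − S − N)/R. If every non-serious event is reported, N = R − S and the share is 0. If none is, N = 0 and the share is (R − S)/R. The article gives none of R, S or N, and the boundary of S is undefined, so the share cannot be narrowed further.

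7. **A related loose end.** Table 1 speaks of the IRB in the singular, while the reporting rule names two boards. If their reporting thresholds differ, the count depends on which board is meant.

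**The case against.** The strongest reply is that the restriction to serious events is inferred from silence. The article says that serious events are reported; it does not say that others are withheld. The outcome definition itself speaks of adverse events, not serious ones, which could point to a wider route such as periodic reports under board rules that a condensed article would not spell out. This stands, and it is why the point is that events may be left out, not that they are. It does not remove the problem: the content of the outcome would then depend on a rule the article does not state, and the definition would still be tied to a regulatory threshold and not to harm.

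It is also fair that some worsening or self-injury may be classed as serious and so counted, and that harm shows up elsewhere, in the symptom scales at all three visits, the referral rate, the Burden interviews and the stopping rules. Acceptability rests too on retention, the Acceptability of Intervention Measure and interviews. These soften the consequence, but none is a count of adverse events.

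A reader might go further and object that the count has no time structure, arm split or denominator. The documents do not support that as an error. Table 1 already fixes the time points for Safety, the Study outcomes section makes 3 months the between-group comparison, and arm and denominator display can properly be left to an analysis plan.

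Finally, widening the count has a cost in comparability. The article describes documentation by staff but no structured elicitation of events. In months 0–3 the intervention arm has up to six counseling sessions while the waitlist arm receives usual care, so events are more likely to be noticed in the intervention arm. This stands and belongs in the fix.

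**Conclusion.** The point holds as an inconsistency between the outcome definition (Table 1 and Implementation outcomes) and the recording and reporting rules (Referral and safety protocols). On the stated text, recorded non-serious events may be left out of the only quantitative safety count.

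The size of the omission is undetermined. It runs from none to all recorded non-serious events, depending on two things the article does not settle: where the line for serious is drawn, and whether non-serious events also reach the boards. A reader might infer that such events are definitely excluded, or that most foreseeable harms will be non-serious. The documents say neither; they name the risks without grading them.

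The consequence is confined to the safety component of acceptability. The primary SSQ-14 comparison and its power are not touched. It is still worth correcting, because a conclusion on safety is intended and the present definition can only make the count smaller than what was recorded, never larger.

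**What to change.** Reconcile Table 1, Implementation outcomes, and Referral and safety protocols so that the safety outcome is all recorded adverse events, given as the number of events and the number of participants with at least one. Show serious adverse events and events reported to a review board as sub-lines, naming the board or boards. Present these by arm at the time points already in Table 1. State which events count as serious for this tabulation, and whether non-serious events are also reported to the boards.

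The cost is small, because the events are already to be documented and no new data collection is required. There are two downsides. The count will look less favourable than one limited to reported events. In addition, the intervention arm has more contacts in months 0–3 at which events can be noticed, so the by-arm comparison should be descriptive, without a test, and should carry that caveat.

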**Psychosocial**				
***Adverse childhood experiences***	Adverse Childhood Experiences International Questionnaire (ACE-IQ) [64]	X		
***Resilience***	Coping Self-Efficacy (CSE) [65]	X	X	X
***Social Support***	Oslo Social Support Scale (OSSS-3) [66]	X	X	X

‡To be evaluated throughout the intervention period

**Table 2 Tab2:** Summary of measures for HIV-related outcomes

Outcome	Subgroup	Measurement type	Specific measures
**HIV treatment engagement**	Participants living with HIV	Self-report (behavioral)	Clinic attendance in past 6 months (noting visit frequency may vary by treatment regimen)
		Clinical (optional, if shared)	Most recent viral load; ART regimen; pharmacy refills/missed doses (if noted); clinic attendance documented in health passport or personal medical record
		Psychosocial (self-efficacy)	HIV Self-Efficacy Questionnaire (HIV-SE) [67] to assess confidence in engaging in care
**HIV treatment engagement**	Participants newly diagnosed during study	Self-report	Date and location of most recent HIV test; linkage to clinic/facility for confirmatory testing; referral source (e.g., study team); ART initiation and timing
**HIV prevention engagement**	Participants not living with HIV	Self-report (baseline eligibility)	Sexual Behavior Practices subscale from WAF Survey [58] (e.g., # of partners, condom use, coercive sex, PrEP use)
		Self-report (follow-up)	Repeat WAF items to assess change: condom use consistency, PrEP uptake, reduction in coercive sex or high-risk behaviors
		Psychosocial (readiness)	HIV Prevention Readiness Measure (HPRM) [8]: subscales on self-efficacy, disclosure, and social support; measures readiness and sustained engagement in prevention

**Table 3 Tab3:** Qualitative implementation process measures

Domain	Definition	Data source
Burden	Risks and benefits associated with participation among counselors and study participants	Qualitative interviews with counselors and participants (post-intervention)
Participant responsiveness	Participant engagement and receptiveness to the intervention	Post-session counselor checklist and logs (during intervention), debrief notes (during intervention)
Content coverage	Emergent discussion of key psychosocial themes (e.g., past GBV, HIV-related stressors)	Session summaries and audio reviews (if available) (during intervention, debrief notes (during intervention)
Barriers and facilitators	Factors affecting delivery and engagement (e.g., stigma, trust, mobility)	Qualitative interviews with counselors and participants (post-intervention), debrief notes (during intervention)
Satisfaction	The extent to which counselors and study participants will participate in the intervention again	Qualitative interviews with counselors and participants (post-intervention), Acceptability of Intervention Measure [63]

#### Mental health outcomes

The primary outcome is symptoms of common mental disorders (CMDs), assessed using the Shona Symptom Questionnaire (SSQ-14) [59]. The SSQ-14 consists of 14 yes/no items assessing psychological distress, with a score ≥ 9 indicating probable CMD. This outcome will be measured at 3 months and analyzed as a continuous variable, consistent with the original Friendship Bench study, which used SSQ-14 scores as a continuous measure to assess symptom reduction overtime [24]. The SSQ-14 was selected as the primary outcome measure because it is a culturally adapted and validated screening tool developed specifically for Zimbabwean and similar Southern African primary care populations. It captures symptoms of CMDs across emotional, somatic, and functional domains, and demonstrated strong psychometric properties in the original Friendship Bench trial [24].

The secondary outcome is depressive symptoms, measured using the Patient Health Questionnaire-9 (PHQ-9). PHQ-9 scores will also be analyzed using both binary and continuous analysis, consistent with the original Friendship Bench trial [24]. Although eligibility for this study includes a PHQ-9 score between 10 and 14, PHQ-9 will also be analyzed as a binary variable using a cutoff of ≥ 11 to estimate the prevalence of probable depression, as done in the original trial [24]. The PHQ-9 was selected as the secondary outcome due to its global recognition and its use in clinical settings in Zambia. Using the PHQ-9 enables broader comparability with global mental health studies and potential clinical integration. Exploratory mental health outcomes include anxiety and PTSD symptoms, assessed with the Generalized Anxiety Disorder (GAD-7) scale and Child PTSD Symptom Scale (CPSS) [61], respectively. CPPS was validated among children and adolescents in Zambia with good internal reliability (*α*> 0.80) [68].

#### HIV outcomes

All HIV-related outcomes (treatment and prevention) are exploratory but will be measured at baseline and at 3- and 6-month follow-up. All HIV-related outcomes (for prevention and treatment) are described in Table 2. We will assess HIV prevention engagement and risk behaviors among participants in our study who are not living with HIV, using a self-reported survey on HIV risk behaviors using measures from the World AIDS Foundation (WAF) Survey [58]. These questions will serve a dual purpose:*Eligibility Screening:* At baseline, a brief risk assessment will be administered during the eligibility screening phase to identify young women who are at heightened risk for HIV acquisition. Items will be drawn from the Sexual Behavior Practices subscale of the WAF, a validated tool for assessing HIV-related risk behaviors in sub-Saharan African contexts [58]. Specifically, we will include questions that assess the number of lifetime and recent sexual partners, frequency of unprotected sex or inconsistent condom use, experiences of coerced or forced sex, and use of pre-exposure prophylaxis (PrEP) or other HIV prevention strategies. These items align with high-sensitivity indicators of HIV risk and have demonstrated discriminant validity among youth populations in Zambia [58].*Follow-Up Assessment:* The same set of risk behavior items will be administered again at follow-up visits (e.g., 3- and 6-month post-intervention) to assess changes in HIV risk behaviors and engagement in HIV prevention strategies (e.g., consistent condom use, PrEP uptake, and reduced exposure to coercive sex).

We will also administer the HIV Prevention Readiness Measure (HPRM) [69] at both baseline and follow-up. The HPRM is a validated instrument originally developed for the HPTN 082 study to assess readiness for and sustained use of HIV prevention strategies such as PrEP among AGYW in sub-Saharan Africa [69]. It includes subscales on self-efficacy, disclosure, and social support, which are strong indicators of behavioral and psychosocial engagement in HIV prevention.

HIV treatment engagement will be assessed among participants living with HIV through both self-reported and clinical measures. We will distinguish between women who are already diagnosed with HIV and those who may be newly diagnosed during the study period.For women already diagnosed with HIV, we will assess:oSelf-reported clinic attendance over the past 6 months, recognizing that visit frequency may vary by treatment regimen and differentiated service delivery model (e.g., 1-, 3-, or 6-month refill cycles).oWhere available, participants will be asked to voluntarily share their health passport or personal medical record to assess additional treatment engagement indicators such as:▪ Most recent HIV viral load▪ ART regimen▪ Pharmacy refills or missed doses (if noted)▪ Clinic attendanceFor women newly diagnosed during the study, we will use the following engagement indicators to assess initial linkage to care:oDate and location of most recent HIV testoWhether and where they linked to a clinic or facility for confirmatory testing and careoWhether they were referred to care by a member of the study teamoWhether ART was initiated, and how soon after diagnosis it began

Lastly, HIV treatment self-efficacy among seropositive participants will be assessed using the HIV Self-Efficacy Questionnaire (HIV-SE) [67], which reflects participants’ confidence in managing their HIV care and may be correlated with treatment engagement.

#### GBV experiences, attitudes, and perceptions

GBV-related experiences, attitudes and perceptions will be measured as exploratory outcomes. Experiences of GBV will be assessed using the WHO Multi-country Study on Women’s Health and Domestic Violence Against Women Instrument [1] (Sections 7–10: physical, sexual, and emotional violence by partners and non-partners), while attitudes and risk perceptions will be evaluated using Section 6 of the same instrument. GBV perceptions will also be measured using Perrin et al.’s Social Norms and Beliefs about Gender-Based Violence Scale [62]. These measures were selected for their strong psychometric properties and relevance to sub-Saharan African contexts. Including both experience- and perception-based measures will allow us to assess participants’ attitudes and beliefs, which may serve as important indicators of GBV risk.

#### Implementation outcomes

We will quantitatively assess feasibility outcomes, acceptability, and fidelity. All feasibility metrics are summarized in Table 3. Acceptability will be measured by evaluating retention rate (i.e., number of participants and lay counselors who drop out of the intervention) and safety (i.e., number of adverse events reported to the Institutional Review Board). To assess the acceptability of the intervention from the perspective of participants, we will use the Acceptability of Intervention Measure [63]. AIM is a 4-item scale that captures participants’ overall perceptions of the intervention’s acceptability, using a 5-point Likert response format. These items assess whether participants found the intervention appealing, satisfactory, and appropriate. Acceptability will also be measured through semi-structured interviews with participants and lay counselors as described below. This mixed-method approach (close- and open-ended items) will provide both quantitative and qualitative data on acceptability and identify areas for improvement in future implementation. All qualitative metrics are captured in Table 3.

Lay counselor adherence to the protocol will be monitored using a fidelity checklist and weekly supervision sessions. Fidelity will capture lay counselors' adherence to core problem-solving therapy techniques. Fidelity will be assessed through audio recordings of counseling sessions, contingent upon participant consent, as individuals may choose to opt out of being recorded. During the initial phase of implementation (within the first 2 weeks), all the sessions will be reviewed in a timely manner to provide formative feedback and support counselor development. A random sample of approximately 20% of recorded sessions will be evaluated thereafter.

Lastly, we will qualitatively assess barriers and facilitators of Friendship Bench implementation via semi-structured interviews on intervention experiences among study participants and lay counselors using relevant domains and constructs from the Consolidated Framework for Implementation Research (CFIR) [70], and the modified CFIR for LMICs [71]. We are hoping that capturing barriers and facilitators would also allow us to qualitatively assess satisfaction and burden (i.e., risks and benefits associated with participation among counselors and clients). We will qualitatively assess the feasibility and acceptability of the intervention through semi-structured interviews with both participants and lay counselors. All lay counselors who delivered the intervention (up to 12 total) will be invited to voluntarily participate in an interview. Additionally, we will conduct up to 15 interviews with participants from each study arm (intervention and delayed control group) to gather diverse perspectives on the intervention experience. To accommodate participants who are not fluent or comfortable communicating in English, interviews will be conducted in local languages (e.g., Nyanja or Bemba) by trained bilingual interviewers. All audio recordings will be transcribed and then translated into English (if applicable) for analysis. To ensure accuracy and cultural validity, a subset of transcripts will undergo back-translation and review by the research team.

We will also qualitatively evaluate content coverage of sessions which will include documentation of whether counselors explore topics such as interpersonal challenges (e.g., family or peer relationships), past (not current) experiences of violence, suicidal ideation or distress, and HIV treatment or prevention challenges. These areas are consistent with known stressors among the target population and align with the intervention’s goals of improving coping and mental health outcomes. Content coverage will be assessed as a process measure (i.e., what topics came up in sessions), and as an implementation determinant (i.e., why some topics were avoided or emphasized), especially based on lay counselor interviews or debriefs. Content coverage will be covered in the following ways:*Lay counselor post-session summary forms:* After each session, lay counselors will complete an open-ended note summarizing the main issues discussed. These can be thematically coded by the research team.*Qualitative debriefs or supervision logs:* Counselors may discuss recurring content during weekly group supervision meetings which can be documented and analyzed for patterns.*Lay counselor semi-structured interviews:* As mentioned above, up to 12 lay counselors will participate in semi-structured interviews which may also capture content coverage discussed.

Participant responsiveness will be qualitatively assessed through multiple sources. First, we will conduct semi-structured interviews with both lay counselors and participants to explore how participants experienced the Friendship Bench sessions, which may give us insight on their level of engagement, perceived relevance of the content, and emotional or behavioral reactions. Second, we will analyze post-session summary notes completed by lay counselors after each session, which include reflections on how engaged the participant appeared, whether they participated in problem-solving activities, and how they responded to the session content. Additionally, study team debrief notes—documenting informal observations and key discussion points during supervision meetings—will be reviewed to triangulate findings and assess patterns of responsiveness across participants. This multi-source, qualitative approach will provide a rich understanding of participant responsiveness and help inform adaptations to enhance engagement in future implementation.

